## Abstract

**Background:**

Patients experience considerable postoperative pain after spinal surgery. As the spine is located at the centre of the body and supports body weight, severe postoperative pain hinders upper body elevation and gait which can lead to various complications, including pulmonary deterioration and pressure sores. It is important to effectively control postoperative pain to prevent such complications. Gabapentinoids are widely used as preemptive multimodal analgesia, but their effects and side effects are dose-dependent. This study was designed to examine the efficacy and side effects of varying doses of postoperative pregabalin for the treatment of postoperative pain after spinal surgery.

**Methods:**

This is a prospective, randomized controlled, double-blind study. A total of 132 participants will be randomly assigned to the placebo (*n* = 33) group or to the pregabalin 25 mg (*n* = 33), 50 mg (*n* = 33), or 75 mg (*n* = 33) groups. Each participant will be administered placebo or pregabalin once prior to surgery and every 12 h after surgery for 72 h. The primary outcome will be the visual analogue scale pain score, total dose of administered intravenous patient-controlled analgesia, and frequency of rescue analgesic administered for 72 h from arrival to the general ward after surgery, subdivided into four periods: 1–6 h, 6–24 h, 24–48 h, and 48–72 h. The secondary outcomes will be the incidence and frequency of nausea and vomiting due to intravenous patient-controlled analgesia. Safety will be assessed by monitoring the occurrence of side effects such as sedation, dizziness, headache, visual disturbance, and swelling.

**Discussion:**

Pregabalin is already widely used as preemptive analgesia and, unlike nonsteroidal anti-inflammatory drugs, is not associated with a risk of nonunion after spinal surgery. A recent meta-analysis demonstrated the analgesic efficacy and opioid-sparing effect of gabapentinoids with significantly decreased risks of nausea, vomiting, and pruritus. This study will provide evidence for the optimal dosage of pregabalin for the treatment of postoperative pain after spinal surgery.

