### Trial design

This will be a single-centre, randomized, prospective, double-blind, superiority clinical trial with four arms. The trial will include three treatment arms where pregabalin will be administered at different doses (25, 50, 75 mg), and one control arm where placebo will be administered. The participants will be equally distributed among the four arms.

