## Statistical methods

### Statistical methods for primary and secondary outcomes

The primary objective of this study is to compare the effect of different doses of pregabalin to placebo on pain relief and the need for additional analgesics during the 72-h period following surgery, at various time points. Additionally, the study aims to assess the incidence of adverse events during this period. Primary outcomes include the VAS pain score, total dose of IV PCA administered, and frequency of rescue analgesic administered. We will use the Kolmogorov–Smirnov test (K-S test) to assess the normality of the primary outcome measure. If the normality assumption is met, we will perform an analysis of variance (ANOVA) analysis; otherwise, we will use the Kruskal–Wallis test for comparison. We will use the Bonferroni’s method for conducting subgroup analysis to account for multiple comparisons. Categorical variables, such as the incidence and frequency of nausea and vomiting caused by IV PCA or the incidence of side effects (sedation, dizziness, headache, visual disturbance, and swelling), will be compared between the groups using the chi-squared test. Statistical analyses will be performed using SPSS 20.0 (IBM, Armonk, NY, USA). In all analyses, *P* < 0.05 will be taken to indicate statistical significance.

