### Methods for additional analyses (e.g. subgroup analyses)

No additional analyses are planned.

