The adverse effects of postoperative pregabalin have not been investigated in detail. Most studies focused on the efficacy and side effects of pregabalin when used preoperatively [25, 27]. Kim et al. [18] reported the incidence of pregabalin side effects until 48 h postoperatively, but the doses of pregabalin used in that study were 75 mg and 150 mg. Our study will focus on the efficacy and adverse effects of postoperative pregabalin at lower doses (25 mg, 50 mg, and 75 mg).

In conclusion, our study will provide evidence on the efficacy of pregabalin for postoperative pain relief after spinal surgery without major side effects even when used at the low dose of 25 mg.

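### The article promises an optimal dose and a 25 mg dose free of major side effects, but a superiority comparison of four unordered arms with 26 to 33 evaluable patients each cannot establish either through a non-significant difference

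*Protocol article*

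**What the plan says.** The protocol article makes two claims about what the trial will deliver. The abstract's Discussion paragraph states: "This study will provide evidence for the optimal dosage of pregabalin for the treatment of postoperative pain after spinal surgery". The last paragraph of the main Discussion expects evidence of efficacy "for postoperative pain relief after spinal surgery without major side effects even when used at the low dose of 25 mg".

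The design and analysis behind these claims are:

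- **Trial design:** a "single-centre, randomized, prospective, double-blind, superiority clinical trial with four arms" (placebo, 25, 50 and 75 mg). No non-inferiority or equivalence margin is given.
- **Statistical methods for primary and secondary outcomes:** the primary objective is to "compare the effect of different doses of pregabalin to placebo on pain relief and the need for additional analgesics". The test is fixed as follows: "If the normality assumption is met, we will perform an analysis of variance (ANOVA) analysis; otherwise, we will use the Kruskal–Wallis test for comparison". Bonferroni's method is named for multiple comparisons, but the pairs are not listed. Nausea, vomiting and side effects are compared by chi-squared tests.
- **Methods for additional analyses:** "No additional analyses are planned".
- **Sample size:** 28 evaluable and 33 randomised per group, powered for an overall four-group difference in PCA usage.

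The abstract's Background says that both the effects and the side effects of gabapentinoids depend on dose, and the Introduction repeats this for adverse effects.

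**The concern.** An optimal low dose has to be supported by an estimate of how benefit and harm change with dose, or by evidence that the lower dose is not meaningfully worse than the higher one. The stated tests ask only whether the groups differ, and they ignore the order of the doses. If 25 mg and 75 mg do not differ significantly, or side-effect rates do not, the result may reflect imprecision alone. The Discussion's last sentence already words the favourable conclusion, so a null comparison could easily be taken as confirming it. At stake are a recommendation of 25 mg as sufficient, and a statement about absence of major harm, that the data would not carry.

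**Working it through.** **Inputs.** From Sample size: f = 0.448, alpha = 0.0167, power 0.95, 28 evaluable and 33 randomised per group, about 15% loss, SD about 10 for PCA usage. From the section on non-adherence and missing data: completers only, with 20% withdrawal expected. Response shapes and side-effect rates in steps 5 and 6 are assumptions, because the article gives none.

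**1. The plan's own figure.** Taking f and alpha as stated, λ = f²N = 0.448² × 112 = 22.5. The noncentral F on 3 and 108 df gives power 0.955 at 28 per group and 0.946 at 27. So 28 per group (112) reproduces, and 28/0.85 = 32.9 gives 33. That power is for some difference among four groups, not for ordering doses.

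**2. Evaluable number.** 33 × 0.85 = 28.05 and 33 × 0.80 = 26.4, so about 26 or 28 per arm, and 33 with no loss.

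**3. Precision of one dose against another.** Half-width = t × √(2/n), in SD units. At n = 28, √(2/28) = 0.267.
- Unadjusted: 1.982 × 0.267 = 0.53 SD.
- Bonferroni over six pairs (an assumption, since the pairs are not listed): 2.688 × 0.267 = 0.72 SD.

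On the planning SD of 10 these are 5.3 and 7.2 units of PCA usage. Power at n = 28 (noncentral t, 108 df):

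| True gap | alpha 0.05 | alpha 0.05/6 |
|---|---|---|
| 0.5 SD | 46% | 21% |
| 0.8 SD | 84% | 62% |
| 1.0 SD | 96% | 85% |

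The gap detectable with 80% power (two-sample t, 54 df) is 0.76 SD at 0.05 and 0.96 SD at 0.05/6. A half-SD loss at 25 mg would be missed 54% of the time unadjusted and 79% of the time with Bonferroni.

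**4. Zero major side effects in an arm.** The upper limit of the two-sided 95% interval is 1 − 0.025^(1/n): 13.2% at n = 26, 12.3% at n = 28, 10.6% at n = 33. If the true rates were 10% and 20% (assumed), a pairwise test at 28 per arm would have 18% power.

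**5. Would a linear dose contrast do better for efficacy?** Omnibus: λ = nΣ(μᵢ − μ̄)², noncentral F(3, 108). Contrast with c = (−3, −1, 1, 3): δ = Σcᵢμᵢ / √(20/n), noncentral t(108). n = 28, two-sided 0.05.

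| Assumed effects at 0/25/50/75 mg (SD) | Omnibus | Linear contrast |
|---|---|---|
| Linear to 0.7 | 61% | 78% |
| Linear to 0.8 | 74% | 88% |
| Only 75 mg: 0, 0, 0, 0.7 | 76% | 69% |
| Plateau: 0, 0.7, 0.7, 0.7 | 76% | 69% |
| Non-monotone: 0, 0.7, 0.7, 0.35 | 72% | 23% |

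The contrast gains for a linear response. It loses something if 25 mg already gives the full effect, and much if the response turns down at the top dose.

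**6. Trend test for side effects.** Simulation with assumed rates of 10/20/30/40% and 28 per arm: Cochran–Armitage trend 80% power, unordered chi-squared 64%.

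**The case against.** The strongest reply is that the plan is aligned with what it mainly asks. The stated objective compares doses with placebo, a superiority framework suits that, and no margin is needed to show that 25 mg beats placebo. The Objectives section asks only about efficacy and safety of varying doses, and providing evidence for a dosage is softer than a guarantee. Bonferroni comparisons are planned, so doses far enough apart can be separated. An ordered contrast or a confidence-interval format might sit in an analysis plan that is not shown, and the statement on additional analyses stands under a template heading whose example is subgroups.

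Much of this stands, and it rules out three stronger readings:

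- A reader might infer that the trial cannot rank doses at all. Step 3 shows 85% power for a 1.0 SD gap even at 0.05/6.
- A reader might infer that a null 25 versus 75 mg comparison is the only route to the closing claim. For efficacy, 25 mg versus placebo is a direct route and is the stated objective.
- A reader might infer that the authors intend to read non-significance as equality. No section says so.

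What does not fall is the mismatch between the two claims and the stated tests. Beating placebo at 25 mg does not make 25 mg optimal, and no planned test can support absence of major side effects at this size.

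**Conclusion.** The concern holds in this form: the article attributes to the design two conclusions, an optimal dosage and a 25 mg dose without major side effects, that its stated tests and size do not support through non-significance. The size of the gap is ±0.53 SD (±0.72 SD with Bonferroni over six pairs) between any two doses at 28 per arm, and an upper limit of 10.6% to 12.3% on a major side effect never observed in 33 to 28 patients. At the 20% withdrawal rate the limit is 13.2%.

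The interval widths assume roughly normal outcomes with a common SD; the Bonferroni figures assume all six pairs. The zero-event limits assume that every treated patient's side effects are counted. The article removes participants with severe reactions from the trial and analyses completers. If that set were also used for safety, the closing claim would be weaker still; the article does not say whether it is.

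A reader might also infer that a linear dose contrast should become the lead efficacy test. The calculations do not support that. Its advantage depends on the response being close to linear, and a significant trend would neither identify an optimal dose nor show that 25 mg suffices.

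**What to change.** 1. Replace the claim in the abstract's Discussion paragraph and the closing sentence of the main Discussion with estimates of each dose versus placebo, for benefit and for each side effect, with confidence limits. State that a non-significant difference between doses will not be read as equal efficacy or as absence of harm.
2. Test side effects, which the article itself calls dose-dependent, with a trend test across 0/25/50/75 mg (Cochran–Armitage), instead of only an unordered chi-squared test. This improves the chance of seeing a dose-related harm. It does not show absence of harm, so the confidence limits are still needed.
3. Add a dose-trend contrast for efficacy as a prespecified supporting analysis beside the dose-versus-placebo comparisons, and amend the statement that no additional analyses are planned.

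The cost is wording and a few lines of analysis specification, with no change to patients, data or treatment. Keeping the efficacy contrast in a supporting role avoids the power loss for plateau and non-monotone responses.

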**Trial registration:**

ClinicalTrials.gov NCT05478382. Registered on 26 July 2022.

**Supplementary Information:**

The online version contains supplementary material available at 10.1186/s13063-023-07438-2.

## Introduction

### Background and rationale

Postoperative pain after spinal surgery is debilitating for the patients due to its severe intensity. As the spine is located at the centre of the body to support body weight, severe postoperative pain hinders upper body elevation and gait, which can lead to various complications, including pulmonary deterioration and pressure sores [1, 2]. Effective control of postoperative pain is important for the prevention of such complications and for fast rehabilitation [3, 4].

Preemptive multimodal analgesia is often performed using acetaminophen and nonsteroidal anti-inflammatory drugs (NSAID) [5, 6]. However, NSAIDs have a risk of complications, such as renal toxicity, bleeding tendency, and cardiac events, limiting their use in the elderly or in patients with pre-existing renal insufficiency [7, 8]. NSAID use following spinal fusion has also been reported to increase the rate of nonunion [9]. In contrast, gabapentinoids including gabapentin and pregabalin are relatively safe for patients with renal or cardiac risk factors, do not hinder fusion after spinal surgery, show opioid-sparing effects, and decrease the adverse effects of intravenous patient-controlled analgesia (IV PCA) [10, 11]. Due to these advantages and their efficacy, gabapentinoids are widely used for the management of postoperative pain after various surgeries [12–14].

Pregabalin binds to the α2-δ protein subunit of presynaptic voltage-gated calcium channels in both the central and peripheral nervous systems, and it has a superior pharmacodynamic and pharmacokinetic profile to that of gabapentin [15]. It is a more potent and more effective analogue of gabapentin [16]. However, gabapentinoids are associated with several adverse effects, including sedation, dizziness, and peripheral oedema, which are known to be dose-dependent [17]. There is currently some controversy regarding the optimal safe dose of gabapentinoids.

### Objectives

The objective of this study is to examine the efficacy and safety of varying doses of pregabalin for the treatment of postoperative pain after spinal surgery.

### Trial design

This will be a single-centre, randomized, prospective, double-blind, superiority clinical trial with four arms. The trial will include three treatment arms where pregabalin will be administered at different doses (25, 50, 75 mg), and one control arm where placebo will be administered. The participants will be equally distributed among the four arms.

## Methods: participants, interventions, and outcomes

### Study setting

This trial will take place at Ajou University Hospital in Suwon, South Korea. The trial protocol has been approved by the Institutional Review Boards of our institution (AJOUIRB-CT-2022–350). This study was registered at ClinicalTrials.gov (National Clinical Trial number: NCT05478382), and the protocol was designed following the guidelines of the Consolidated Standards of Reporting Trials and Standard Protocol Items: Recommendations for Interventional Trials (SPIRIT) (Additional file 1). We plan to begin trial recruitment in October 2022, and the planned study period will be 4 years. A total of 132 participants will be enrolled after recruitment is announced, and allocation will be performed by stratified block randomization.

### Eligibility criteria

Patients undergoing spinal surgery for degenerative lumbar disorders will be recruited from the Department of Orthopaedic Surgery, at Ajou University Hospital. Identified patients will be approached for inclusion in the study based on the inclusion/exclusion criteria described below.

Inclusion criteria are as follows: age 19 years or older, patients undergoing spinal surgery for degenerative lumbar disorders, and voluntary agreement to participate in the study after receiving sufficient explanation.

Exclusion criteria are as follows: minors under the age of 19 years, patients assigned to American Society of Anesthesiologists classification class 3–6, previous frequent dizziness or headaches, active alcohol or drug usage, having taken any analgesics daily or within 48 h before surgery, impaired renal (glomerular filtration rate < 60 mL/min/1.73 m^2^) and/or hepatic function (Child Pugh classification B and C), diagnosed with and treatment for anxiety or depressive disorders, and coverage from worker’s compensation insurance or car insurance.

Patients with severe adverse reactions to our drug of interest, such as dizziness, drowsiness, or peripheral oedema, will be excluded. Patients with any postoperative complications including infection, nerve injury, hematoma, metal implant-related problems, and death, will also be excluded.

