### Criteria for discontinuing or modifying allocated interventions

Participants who present with severe drowsiness, dizziness, visual disturbance, or swelling that precludes the use of pregabalin will discontinue the trial and stop taking their allocated treatment. Participants who develop infection, nerve injury, hematoma, or metal-related complications following surgery or those who request discontinuation will also be excluded from the trial.

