## Assignment of interventions: allocation

### Sequence generation

All patients will be randomized to one of the following four groups at a 1:1:1:1 ratio one day prior to surgery: P0 (*n* = 33), P25 (*n* = 33), P50 (*n* = 33), and P75 (*n* = 33) groups. The assignment will be conducted by computer-generated random sequence with block randomization, stratified by sex and age (< 65 and ≥ 65 years). Based on the potential risk of age and gender having an impact on the pain relief and side effect outcomes after surgery, as suggested by previous literature, we performed stratification accordingly [19]. To maintain an equal allocation of participants to each of the four treatment groups, we will use a block size of 4 (one allocation for each treatment group within a block). The generated sequence will be masked from the primary investigators and will be recorded in the randomization list.

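### Entry is open to any degenerative lumbar operation, but the primary tests use arm alone: adjusting for planned procedure would be a cheap, optional gain in precision

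*Protocol article*

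**What the plan says.** All references are to the protocol article.

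- **Eligibility criteria.** Entry requires "age 19 years or older, patients undergoing spinal surgery for degenerative lumbar disorders, and voluntary agreement to participate". No procedure, number of levels or use of instrumentation is specified. The same section removes patients with complications that include "infection, nerve injury, hematoma, metal implant-related problems, and death", and the section on discontinuing the intervention lists "infection, nerve injury, hematoma, or metal-related complications following surgery", so operations with implants are expected. The introduction also argues for gabapentinoids partly because they do not hinder fusion.
- **Sequence generation.** Allocation is 1:1:1:1 with 33 per arm, by "computer-generated random sequence with block randomization, stratified by sex and age", in blocks of 4. The reason given is "Based on the potential risk of age and gender having an impact on the pain relief and side effect outcomes after surgery". Extent of surgery is not mentioned.
- **Statistical methods for primary and secondary outcomes.** VAS score, PCA dose and rescue frequency are compared by ANOVA if a normality test is passed and by Kruskal–Wallis otherwise. No covariate is named, not even the two stratification factors.
- **Methods for additional analyses.** "No additional analyses are planned".
- **Sample size.** 112 patients (28 per group) from f = 0.448, alpha 0.0167 and power 0.95, raised to 132 for about 15% loss. The SD behind the effect size is about 10.

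**The concern.** The primary outcomes measure pain and analgesic use in the 72 hours after an operation whose extent the criteria leave open. If larger operations hurt more, surgery type adds variance to every primary outcome. The protocol stratifies on age and sex because they may affect pain relief and side effects. The same reasoning extends to the operation itself, yet this enters neither the randomisation nor the analysis.

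Two things are at stake. Intervals for the dose comparisons are wider than they need be. And in an individual trial where the arms differ in surgical mix, part of the observed difference between arms comes from that mix and not from the drug.

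**Working it through.** **Inputs from the protocol:** four arms, 33 randomised per arm, 28 per arm for analysis, f = 0.448, alpha 0.0167, SD about 10.

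**Assumed, because the protocol gives neither:** share p of fusion (or instrumented) operations, 30–90%; difference d in mean outcome between fusion and decompression-only patients, 0.5–1.0 within-type SD.

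**1. The plan's own figure.** Noncentral F with k = 4 and noncentrality N·f² = 112 × 0.448² gives power 0.955 at alpha 0.0167, and 28/(1 − 0.15) rounds up to 33. The stated size reproduces from the stated f and alpha. Whether those two inputs are right is a separate question.

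**2. Variance explained by surgery type.** R² = p(1−p)d² / (1 + p(1−p)d²). The equivalent extra sample is 1/(1−R²) − 1, which equals p(1−p)d².

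| p | R², d = 0.5 | R², d = 1.0 | extra patients |
|---|---|---|---|
| 30% | 5% | 17% | 5–21% |
| 50% | 6% | 20% | 6–25% |
| 80% | 4% | 14% | 4–16% |
| 90% | 2% | 8% | 2–9% |

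**3. Chance imbalance at 33 per arm** (binomial counts in four arms). Probability that the largest gap between any two arms is at least 20 points: 38% at p = 50%, 30% at p = 30%, 18% at p = 80%, 4% at p = 90%. For placebo against one given dose, a gap of at least 20 points occurs in 11% of trials at p = 50%.

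**4. What a gap does to a contrast.** A 20-point gap shifts the difference between two arms by 0.20 × d, that is 0.1 SD at d = 0.5 and 0.2 SD at d = 1.0. The standard error of that difference is √(2/33) = 0.25 SD. On the protocol's scale (SD 10) the shift is 1–2 units, against 105.2 − 95.3 = 9.9 between the extreme means used for the sample size.

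**5. Type I error** (simulation, 28 per arm, p = 50%, no dose effect, test at 0.05). Here the surgery effect is in units of total SD. The unadjusted ANOVA rejects in about 0.05 of all trials. In trials with a largest gap of about 25 points or more, it rejects in 0.060 for an effect of 0.5 SD and 0.096 for 1.0 SD. ANCOVA on surgery type stays at about 0.05 in the same trials.

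**6. Power at N = 112** (p = 50%, f = 0.448, alpha 0.0167).
- If SD 10 already includes the surgical mix, power is about 0.95 unadjusted, and 0.966 (0.5 SD) or 0.990 (1.0 SD) adjusted.
- If SD 10 came from a more uniform population, the variance rises by a factor of 1 + 0.25d². Unadjusted power is then 0.940 at d = 0.5 and 0.889 at d = 1.0, and the N needed is 120 and 136.

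**The case against.** The strongest reply is that an unadjusted comparison of randomised arms is valid. That stands: overall type I error is preserved.

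A reader might go further than the point made here and infer that imbalance in surgery could mimic or hide a dose effect. The documents do not support that reading. Even a 20-point gap moves a contrast by less than one standard error at the assumed effects, and by 1–2 units where the plan designs for 9.9.

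The inputs are also open. No section lists operations or mentions decompression, and the mix is inferred from an unrestricted criterion. The references to implants and fusion fit a mostly instrumented population just as well, and then both imbalance and variance explained are small. Nor does any section say how strongly surgical extent drives pain, or that it matters more than sex or age. This stands, and it is why the size is given as a range reaching down to 2%.

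Finally, covariates are often left to an analysis plan, the statement that no additional analyses are planned sits under a heading about subgroups, and broad entry serves generalisability. In part this stands. Nothing in the protocol forbids adjustment, and entry need not be narrowed. But the protocol does name its primary tests, and the named fallback, Kruskal–Wallis, cannot take a covariate. Suggesting a better-specified test is therefore fair comment on what is written.

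**Conclusion.** The point holds as a matter of efficiency. The criteria allow operations of differing extent, and the stated analysis recovers none of the variance that this creates. It also leaves out sex and age, although the randomisation uses them.

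Under the assumed ranges (fusion share 30–90%, difference 0.5–1.0 SD), adjustment would be worth about 2–25% more patients and would remove a modest conditional error in unbalanced trials. If nearly all patients have instrumented surgery, or if extent has little effect on these outcomes, the gain is close to nil. No invalid inference or systematic bias is shown. It is an optional, cheap improvement.

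**What to change.** Record the planned procedure (instrumented/fusion versus decompression only) before surgery, so that treatment cannot influence it. Before unblinding, prespecify it together with sex and age group as covariates:

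- VAS and PCA volume: a linear model (ANCOVA) with arm, planned procedure, sex and age group.
- Number of rescue administrations: a count model with the same terms.
- Non-normal outcomes: a rank-based ANCOVA, or the linear model with robust standard errors, in place of Kruskal–Wallis.

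The randomisation scheme and the entry criteria can stay as they are. The cost is one extra baseline field and a slightly more complex model. No further patients or procedures are needed.
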